### Assignment of interventions: blinding

#### Who will be blinded {17a}

This study will be a double-blinded clinical trial. Patients will be blinded to the study because they will receive the intervention after they have been put under general anaesthesia. Members of the research team involved in data collection and analysis will be masked to group allocation. The treating anaesthesiologist and surgeon will not be blinded.

#### Procedure for unblinding if needed {17b}

Allocation of a participant will be revealed immediately if there is a clinical concern, i.e. if the patient met criteria for discontinuing study protocol (part 11b).

### Data collection and management

#### Plans for assessment and collection of outcomes {18a}

Data collection will occur at three distinct time points (pre-operative, intra-operative, and post-operative). Data will be collected from both electronic and paper patient records and directly from the patient by means of completing a questionnaire. The same members of the research team (blinded to the intervention) will collect all peri-operative data. Prior to participant enrolment, data collectors will receive specific training from the principal investigator (DB), regarding data handling, collection, and storage; case record form; and QoR-15 questionnaire completion process. This will ensure high quality data collection during the clinical trial. After completion of patient recruitment, data will be transcribed onto Microsoft Excel, and subsequently, the raw data sheet will be thoroughly investigated by the principal investigator for any accidental input of duplicate measurements and/or for any missing key data points. Furthermore, the principal investigator will be blinded to the patient group and groups will only be unblinded after completion of patient recruitment and statistical analysis of the raw data is ready.

#### Plans to promote participant retention and complete follow-up {18b}

Study participants will receive a comprehensive patient information leaflet (PIL) about the trial. A member of the research team will explain this PIL, study set-up, and the study interventions. The importance of completion of postoperative follow-up will be stressed to all participants.

#### Data management {19}

All patient data collected will be handled in accordance with European Union General Data Protection Regulations (EU 2016/679). Initially, data will be collected manually and then transcribed onto Microsoft Excel. Data collected in each clinical site will be stored securely on a password-protected desktop computer, stored in a locked office in the Department of Anaesthesiology at the respective hospital, such that only investigators assigned to data input, processing, and analysis will have access. Data will be collected directly from source documents into the de-identified encoded paper case record form (CRF) and subsequently entered into the electronic CRF. In accordance with local and international regulations, a copy of the original hardcopy CRF will be stored in a locked cabinet/office accessible to authorised personnel only.

#### Confidentiality {27}

All research data will be stored using a study identification number for each patient. An identifiable patient data page reporting the assigned patient identification code will be stored separately also in a locked cabinet/office (accessible to authorised personnel only) in order to record in-hospital outcomes, supply missing data points and to allow potential monitoring visits by national coordinating investigators. This data page will only be made available to members of the research team responsible for data input and the principal investigator. No patient identification details will be reported in any future publications.

#### Plans for collection, laboratory evaluation, and storage of biological specimens for genetic or molecular analysis in this trial/future use {33}

Not applicable, no samples will be collected.

### Statistical methods

#### Statistical methods for primary and secondary outcomes {20a}

The collected raw data will be inspected for any errors. These include but are not limited to, double entry errors, missing data, and data that was incorrectly entered. Data will be recorded in Excel™ (Microsoft, Redmond, WA, USA) and subsequently imported into GraphPad Prism version 9.3.1 (GraphPad, Salt Lake City, UT, USA) for statistical analysis. All data will be stored according to EU Directive 2019 on General Data Protection Regulations. Data will be inspected and tested for normal distribution according to the Shapiro-Wilk test and quantile-quantile (QQ) plot graph as appropriate. Normally distributed data will be compared between study arms using the unpaired *t* test, whereas non-normally distributed data will be compared using Mann-Whitney *U* test. Fisher’s exact test was used for comparing categorical data. All data will be summarised as mean (SD), median (25–75% range), and *n* (%) as appropriate, and *p* value < 0.05 will be considered statistically significant.

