#### Sample size {14}

The primary outcome of this study will be the QoR-15 score at 24 h postoperatively. This score rates 15 subjective, patient-reported parameters about their recovery on a scale of 0–10. Therefore, the minimum possible score is 0, and the maximum possible score is 150. The established minimum clinically important difference in QoR-15 is 6.0 [14], and the mean SD of QoR-15 scores after major surgery is in the order of 8–16. Taking an SD of 8, and assuming type I error = 0.05 and type II error = 0.2 (80% power to detect this difference), then *n* = 28 patients will be required in each group. To accommodate for participants who may withdraw from the study, we will aim to recruit *n* = 30 patients to each study arm, i.e. *n* = 60 in total.

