#### Methods in analysis to handle protocol non-adherence and any statistical methods to handle missing data {20c}

Our expectation is that very few patients will be lost to follow-up during their inpatient stay due to protocol adherence strategies as mentioned above. Therefore, we expect missing data will be at a minimum when analysing the primary outcome. Multiple imputation will be used if a statistical method is needed to account for missing data in terms of secondary outcomes.

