Bolus injection of a local anaesthetic followed by continuous infusion has been the standard technique for fascial plane catheters such as PVB and ESP for post-thoracotomy analgesia [7, 22]. However, it has been shown in paravertebral blocks that the range of anesthetised dermatomes becomes gradually narrower when the local anaesthetic is administered at a constant rate [23]. Theoretically, the addition of a bolus injection of local anaesthetic to continuous infusions may maintain the range of anesthetised dermatomes; however, this theory has not been elucidated in clinical trials relating to ESP blocks. In this study, we hypothesise that programmed intermittent erector spinae plane bolus of levobupivacaine will maintain a wider sensory block and improved quality of recovery compared with continuous infusion.

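### Time to first postoperative IV opioid is assigned to a t test or Mann-Whitney test with no time-to-event method and no rule for patients who never receive an IV opioid

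*Protocol article*

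**What the plan says.** Time to the first postoperative IV opioid is one of the secondary outcomes in the protocol article (Secondary outcome measures). It carries no time frame and no rule for a patient who receives none.

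Section {20a}, whose heading covers primary and secondary outcomes, fixes the tests:

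- Numeric data: "Normally distributed data will be compared between study arms using the unpaired *t* test, whereas non-normally distributed data will be compared using Mann-Whitney *U* test".
- Categorical data: Fisher's "exact test was used for comparing categorical data".
- Summaries: "All data will be summarised as mean (SD), median (25–75% range), and *n* (%) as appropriate".

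Section {20c} adds: "Multiple imputation will be used if a statistical method is needed to account for missing data in terms of secondary outcomes". It does not distinguish a value that was not collected from an event that did not happen. Kaplan-Meier, log-rank, Cox regression and censoring appear nowhere in the article.

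**The concern.** A t test or Mann-Whitney test needs a value for every patient it includes. A patient who never receives an IV opioid has no time to the first one, and on this outcome that patient has done best.

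The easiest course is to compare the times that exist. The null hypothesis then becomes equality of times among patients who did receive an IV opioid. That conditions on an event after randomisation which the treatment may prevent, so the two groups compared are no longer the randomised ones. A benefit that consists of avoiding IV opioids largely drops out of the comparison.

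The direction can also change. The Discussion reports, for paravertebral blocks, that "the range of anesthetised dermatomes becomes gradually narrower when the local anaesthetic is administered at a constant rate". If something similar held here and boluses mainly prevented late requests, the recorded times left in the bolus arm would be mostly early ones, and that arm would seem to need opioids sooner.

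**Working it through.** **The plan's own figure.** The sample size section uses "The established minimum clinically important difference in QoR-15 is 6.0", "Taking an SD of 8" and "assuming type I error = 0.05 and type II error = 0.2 (80% power to detect this difference". With a two-sided test (sidedness is not stated), n per arm = 2 × (1.96 + 0.842)² × 8² / 6² = 27.9, so 28, as the article says. That figure rests on QoR-15 and is not in dispute here.

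**Inputs for this outcome.** From the article: 30 per arm and 1:1 allocation. Assumed:

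- a 48 h horizon, borrowed from the opioid-consumption outcome;
- a two-sided 5% level;
- the share needing an IV opioid in each arm, continuous infusion (CI) versus programmed bolus (PIB), because the documents give none.

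**What recorded times show: constant hazards, 80% vs 50% by 48 h.**

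- Hazards: CI −ln(0.20)/48 = 0.0335 per h; PIB −ln(0.50)/48 = 0.0144 per h. Hazard ratio: ln 0.50 / ln 0.20 = 0.43.
- Expected patients with a time: 24 of 30 (CI) and 15 of 30 (PIB). Left out: 6 and 15, all of them event-free.
- Median over all patients: CI ln 2 / 0.0335 = 20.7 h; PIB 48 h.
- Median among users: CI −ln(0.60)/0.0335 = 15.2 h; PIB −ln(0.75)/0.0144 = 19.9 h.

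A gap of about 27 h shrinks to under 5 h.

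**Late-only benefit: 40% by 6 h in both arms, then 80% vs 50% by 48 h.**

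- Hazard to 6 h, both arms: −ln(0.60)/6 = 0.0851 per h.
- Median over all patients: CI 6 + ln(0.60/0.50) / [ln(0.60/0.20)/42] = 13.0 h; PIB 48 h.
- Median among users: CI 6.0 h (40% is half of 80%); PIB −ln(0.75)/0.0851 = 3.4 h.

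The bolus arm does better overall, but among users its times are shorter.

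**Power by simulation** (4,000 trials per row, 30 per arm, follow-up ended at 48 h):

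| Need by 48 h, CI vs PIB | Log-rank, all patients | Mann-Whitney, never-users tied at 48 h | Mann-Whitney, recorded times only |
|---|---|---|---|
| 80% vs 50% | 75% | 71% | 12% |
| 80% vs 40% | 93% | 91% | 13% |
| 70% vs 35% | 81% | 78% | 8% |
| 90% vs 60% | 87% | 81% | 22% |
| 95% vs 75% | 78% | 69% | 27% |
| 80% vs 80% (null) | 5.0% | 4.7% | 4.4% |
| Late-only benefit | 46% | 24% | 31%, essentially all in the wrong direction |

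Repeat runs agreed within simulation error; for the late-only row, the recorded-times test was significant in 28% to 31% of trials.

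**Other models** (2,000 trials each). With hazard ratio 0.5 and 90%, 70% or 50% of CI patients needing an IV opioid, power for recorded times, tied rank and log-rank was 17/57/66%, 8/49/53% and 6/39/40%. With equal timing among users and only the share differing, 90% vs 60% gave 5/53/72%, and a modest 95% vs 85% gave 6/11/16%.

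Multiple imputation was not simulated.

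**The case against.** A reader might infer that the plan drops never-users or gives them an imputed time. The article says neither. The imputation sentence in {20c} is conditional, and a chart showing that no IV opioid was given is not, on its face, missing data.

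Nor does {20a} rule out a sound analysis. A Mann-Whitney test with never-users tied at the longest rank is still a Mann-Whitney test. Against log-rank it loses 4, 2, 3, 6 and 9 points in the five constant-hazard rows with a benefit. What is missing on that reading is a coding rule.

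The scenarios are also favourable to the point. The constant-hazard pairs in the table imply hazard ratios of about 0.32 to 0.46, which is large for two arms given 25 mg levobupivacaine every 2 h that differ only in delivery. For 95% vs 85%, even log-rank reaches only 16%. The 6 h cut is invented. The Discussion speaks of dermatomes in paravertebral blocks, not of when opioids are requested, and says the theory is untested for this block. Total opioid consumption, also a secondary outcome, can count non-users as zero, so the trial would not be blind to opioid avoidance.

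Finally, a condensed article may leave a censoring horizon to a fuller document.

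Most of this stands and limits the size of the point. It does not remove it. The article is not silent: it assigns tests and summaries to all outcomes, and those have no place for an event that never happens. The tied-rank version is permitted but not stated, needs a common horizon, and loses 22 points (46% vs 24%) in the late-benefit row.

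**Conclusion.** The point holds for one secondary outcome. The stated method does not suit a time that some patients may never reach, and the result depends on an unstated choice about them.

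- If only recorded times are compared: about 12% power against 75% under 80% vs 50%, and possible reversal if the benefit is late.
- If never-users take the longest tied rank: a loss of about 2 to 9 points under constant hazards and about 20 to 25 under the late-only scenario.
- If nearly every patient receives an IV opioid: no material consequence.

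All of these rest on assumed rates, an assumed 48 h horizon and a two-sided 5% test. The article gives no rate, and its analgesia protocol is a figure that is not available here. The late-only scenario shows that reversal is possible, not that it is expected. The documents do not support saying that the trial will discard or impute its best outcomes. Type I error stayed near 5% for all three tests in the null scenario. The primary QoR-15 analysis and the 60-patient sample size are unaffected.

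**What to change.** In {20a}, state that time to first postoperative IV opioid is analysed in all randomised patients by Kaplan-Meier estimates and a log-rank test, with a Cox hazard ratio and 95% confidence interval. Patients with no IV opioid are censored at a stated horizon, such as 48 h, or at discharge or withdrawal if earlier. In {20c}, state that receiving no IV opioid is an observed outcome and is not imputed.

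If Mann-Whitney is kept, state that patients event-free at the horizon share the longest tied rank.

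The cost is one or two sentences, with no extra patients. Opioid administration and length of stay are already outcomes, so the times should be on record. The small downside is that a Kaplan-Meier curve and a hazard ratio replace a simple mean or median. The rule should be fixed before unblinding, because choosing it afterwards could change the conclusion.

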#### Interim analyses {21b}

There are no interim analyses planned.

#### Methods for additional analyses (e.g. subgroup analyses) {20b}

There are no subgroup analyses planned.

#### Methods in analysis to handle protocol non-adherence and any statistical methods to handle missing data {20c}

Our expectation is that very few patients will be lost to follow-up during their inpatient stay due to protocol adherence strategies as mentioned above. Therefore, we expect missing data will be at a minimum when analysing the primary outcome. Multiple imputation will be used if a statistical method is needed to account for missing data in terms of secondary outcomes.

#### Plans to give access to the full protocol, participant-level data, and statistical code {31c}

The assembled data collected will be retained for a maximum 5 years after completion of analysis. A completely de-identified data set will be provided where appropriate upon reasonable request and in agreement with the principal investigator and data protection officer.

### Oversight and monitoring

#### Composition of the coordinating centre and trial steering committee {5d}

The study steering committee will meet monthly to assess progress, address any ongoing organisational or logistical issues, and to consider any adverse effects. A research leader for each clinical site will provide monthly reports to the principal investigator.

#### Composition of the data monitoring committee, its role and reporting structure {21a}

A data protection impact assessment (DPIA) screening tool for this study was completed and analysed by the hospital’s data protection officer (DPO). The decision of the DPO was that no data monitoring committee (DMC) was required for this study as it poses a low risk to the rights and freedoms of natural persons. Therefore, a formal DPIA was not required. Furthermore, a DMC was not appointed, due to the expected expeditious inclusion of participants to this trial. Data collection is expected to be completed in nine to twelve months and minimal inherited risks are associated with this trial.

#### Adverse event reporting and harms {22}

Any unexpected complications which may arise during this trial will be documented and reported to the principal investigator, attending anaesthesiologist, surgical consultant, and to the relevant hospital patient safety officer.

#### Frequency and plans for auditing trial conduct {23}

During this study, an initial auditing process may be conducted using a risk-based approach. This would initially involve focusing on the hospital which may have the largest number of enrolment and/or lost to follow-up rates. The auditing process would include exploring datasets and analysing them for accuracy, missing data, duplicate data and adherence to data protection guidelines. This process would be conducted by an independent reviewer with no involvement with this trial (e.g. research nurse who is affiliated with the clinical site but is not involved with this specific trial).

A research nurse affiliated with the department of anaesthesia at MMUH but who is not involved in this trial may undertake an audit involving the exploration of datasets from both institutions. This would be precipitated by risk indices including high rates of dropout rates.

#### Plans for communicating important protocol amendments to relevant parties (e.g. trial participants, ethical committees) {25}

We define a substantial modification of the study protocol as changes which may affect the outcome of the study or patient safety. Such changes include the following: any modification to the aims of the study, study design, and the inclusion or exclusion criteria or any alternations of the study interventions (e.g. using new procedural equipment or conducting any intervention which deviates from the original description). Any amendment will be agreed upon the principal investigator of this trial and will seek approval from the Ethics Committee/IRB. Minor changes of the protocol include any administrative changes or alternation of the analgesia plan that do not impact patient safety nor the conduct of the trial (e.g. changes to anti-emetic medications). The Ethics Committee/IRB may be notified of minor changes at the discretion of the principal investigator.

#### Dissemination plans {31a}

The results from this clinical trial will be fully disclosed by means of publication in an international peer-reviewed journal and by presentation at national and international scientific meetings. Both positive and negative results will be disclosed.

## Discussion

In conducting this randomised control trial, we aim to investigate the efficacy, in terms of quality of recovery, of erector spinae plane catheters using programmed intermittent bolus regimes compared to continuous infusion regimes. Fascial plane blocks including the ESP block have become increasingly popular in recent times, and their use has been reported in a variety of thoracic, spinal, and abdominal surgeries fascial where they may have a role in terms of improving postoperative pain relief, quality of recovery, and patient satisfaction [6, 16–18]. The increase in popularity in fascial plane blocks could be due to a combination of enhanced ultrasound technology and subsequently better understanding of the sonoanatomy of fascial planes and surrounding structures [19]. A fascial plane block is a regional anaesthesia technique in which the space between two fascial layers is the target. The major advantage of fascial plane blocks when compared to neuraxial anaesthesia techniques are their ease of performance and better inherent safety profile. While the exact mechanism of action of ESP is the subject of ongoing debate, its analgesic effects for lumbar surgery are believed to derive from the spread of the local anaesthetic agent to the dorsal and ventral rami of spinal nerves via paravertebral spread-by-proxy [20]. Single-shot truncal regional anaesthesia techniques are restricted by the limited duration of analgesia; catheter techniques can offer the potential benefit of prolonged analgesia. Previous studies using catheter techniques for MITS have used the traditional end points of opioid consumption and pain scores to assess efficacy [21]. The VAS is an imperfect scale without psychometric evaluation that overlooks the individual components of recovery and is prone to overrating [15]. Defining success in regional anaesthesia is multifactorial, and using patient-centred, population-centred, healthcare-centred, and training-centred outcomes may be more beneficial. The QoR-15 can be an advantageous outcome measure in clinical trials and for assessing the impact of changes in health care delivery for quality assurance purposes [15]. To the best of our knowledge, there are no randomised controlled trials comparing continuous infusion versus intermittent bolus strategies for erector spinae plane block for MITS in terms of patient-centred outcomes such as quality of recovery.

Bolus injection of a local anaesthetic followed by continuous infusion has been the standard technique for fascial plane catheters such as PVB and ESP for post-thoracotomy analgesia [7, 22]. However, it has been shown in paravertebral blocks that the range of anesthetised dermatomes becomes gradually narrower when the local anaesthetic is administered at a constant rate [23]. Theoretically, the addition of a bolus injection of local anaesthetic to continuous infusions may maintain the range of anesthetised dermatomes; however, this theory has not been elucidated in clinical trials relating to ESP blocks. In this study, we hypothesise that programmed intermittent erector spinae plane bolus of levobupivacaine will maintain a wider sensory block and improved quality of recovery compared with continuous infusion.

We acknowledge some limitations to this protocol including the fact that the treating anaesthesiologist will not be blinded to the group allocation as they will be required to perform the block. However, the primary will be measured 24 h postoperatively by researchers blinded to the group allocation, thus maintaining blinding of data. We acknowledge that for some patients having MITS their recovery will continue beyond 48 h postop; however, the acute postoperative pain following MITS is diminished by day 3, and many of our patients will be discharged home at this stage. Length of stay and postoperative complications will continue to be observed until patient discharge. ESP catheters will be placed under general anaesthesia; therefore, formal dermatomal assessment of block function will not be possible, and we will not be formally testing block effectiveness. However, the practice of placing these catheters under ultrasound guidance after induction of general anaesthesia is in line with common clinical practice, and therefore, our findings should still be applicable to widespread clinical practice. Assessment of preoperative QoR-15 will not be undertaken in this study. Therefore, we will not have a baseline from which to compare postoperative QoR-15 scores. Nonetheless, QoR-15 was specifically intended for postoperative use, and we will apply this scoring tool equally to both randomised groups. Furthermore, the accuracy of QoR-15 in the immediate pre-operative period has been debated [24]. By focusing on patient-centred outcomes in our trial design, we hope to explicate whether the use of programmed intermittent regimes of delivery of levobupivacaine to the erector spinae plane will result in an improved quality of recovery compared with continuous infusion.

